| 
Methodology:
 
This is a Phase 1/2 study to evaluate the safety and potential efficacy of agenT-797, an unmodified, allogeneic iNKT cell therapy, in patients with moderate to severe ARDS secondary to SARS-CoV-2 or influenza, either with intubation or at high risk to be intubated, as determined using Berlin definition(s) (ARDS 2012).
 
Completed: Part 1 will employ a standard 3+3 dose escalation design of agenT-797. All patients will receive a single infusion of agenT-797. Patients will also receive other treatments and supportive care per discretion of the Principal Investigator. Once the maximum tolerated dose of agenT-797 has been cleared in Part 1, an Expansion Cohort will be opened. A Safety Monitoring Committee (SMC) will be established to assess safety and decide on escalation to next cohort and expansion dose, as well as any protocol modification to include less severe cases.
 
Part 2 (Expansion) of the study will evaluate an additional cohort in up to 15 patients:
 
 
Cohort 4 – patients with moderate to severe ARDS secondary to SARS-CoV-2 or influenza, according to Berlin definition, who are on mechanical intubation
 
 
The SMC will continue to review safety.
 
Screening:
 
Prior to any Screening activities, the patient (or legal representative) must sign an informed consent form and will proceed to undergo full screening procedures to determine eligibility. Full human leukocyte antigen-typing (blood) will also be performed.
 
Eligible patients will be treated with agenT-797 on Day 1. Assessments will be obtained through Day 32 or until discharge from hospital. Safety follow-up will occur 30 days after discharge, the patient to then be contacted regarding serious adverse events (SAEs) and to confirm survival up to 6 months after hospitalization.
 |                                                                                                                                                                                   |

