### **4.7.2. Patient Exclusion Criteria**

For inclusion in the trial, patients must have none of the following exclusionary criteria. No waivers to exclusion criteria will be permitted:

1. Currently participating and receiving study therapy of an investigational agent that is not registered for any other indication
2. Life expectancy of  $< 1$  month
3. Clinically significant cardiomyopathy
4. Pre-existing respiratory disease, such as significant chronic obstructive pulmonary disease requiring home oxygen, hospitalization, or systemic steroid use during the past year.
5. "Significant" pulmonary hypertension as mean pulmonary artery pressure  $\geq 20$  mmHg and evidence of right ventricular dysfunction or enlargement

6. Receipt of vaccines containing live virus within 4 weeks prior to first dose of study treatment
7. Known hypersensitivity to donor-derived cell therapy or their preservation solution
8. Active systemic bacterial or fungal infection or viral co-infection with the exception of:
  - a. Patients with rhinoviral infection (common cold) are permitted to participate
  - b. Patients on treatment and/or ongoing improvement with minor common infections (e.g., urinary tract infection, minor skin infections) are permitted to participate
  - c. Patients with both SARS-CoV-2 and influenza (co-infection) are permitted to participate
9. Pregnant or lactating women
10. **After implementation of Amendment 7:** Presence of multiorgan dysfunction syndrome; no organ failure should be seen other than the organ of interest, which is the lung

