### **8.1.6. Recording of Adverse Events/Serious Adverse Events**

The Principal Investigator is responsible for ensuring that all AEs are recorded on the CRF during the study. All SAEs must be reported on the AE form in the CRF. All AEs, non-serious and serious, related or unrelated, need to be recorded from the time of ICF signature through 30 days, and 6 months in the Safety Follow-up period, after infusion, and followed up until resolution, if feasible ([Section 4.10](#)).

AEs will be categorized as SAEs, AESIs, or DLTs, as applicable, and reported based on applicable guidelines ([Section 8](#)).

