|                                                                                                                                                                  | aeruginosa , Klebsiella pneumoniae , and fungal infections)                                                                                                                                                                                           | infections during follow-up period                                                                                                                                                                                 |
| 
 
To evaluate whether iNKT cells improve lung fitness through assessments of respiratory function
 
                | 
 
Clinical and respiratory function assessments
 
Change in pulmonary involvement based on X-ray and/or computed tomography (CT) scans, as available
 
Health of lung epithelial cells (RNA analysis)
 
 | 
 
Listing of clinical and respiratory function assessments
 
Listing of change in pulmonary involvement
 
Listing of health of lung epithelial cells
 
 |
| 
 
To explore whether iNKT cells promote viral resolution without lung fibrosis in SARS-CoV-2 (COVID-19) patients
 
 | 
 
Time from dosing to viral clearance
 
Fibrosis signs based on X-ray and/or CT scans and respiratory function assessments
 
                                                                                   | 
 
Median time from dosing to viral clearance
 
Listing of fibrosis signs
 
Listing of respiratory function assessments
 
                               |

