### 4.5 Analysis Sets

Three subject analysis sets are defined for the study analyses, as follows:

- **The All Subject Analysis Set** will include all patients who have completed informed consent, irrespective of the study treatment administered. This analysis set will be used for the disposition summary and the listing of study populations.
- **The Safety Analysis Set** will include all patients who received agenT-797. This analysis dataset will be used for safety analysis and all listings other than listings of subject disposition and study populations.
- **The Dose-Limiting Toxicity Analysis Set** will include all patients who either experienced a DLT within 28-day observation or completed study treatment and 28-

day observation for DLT without experiencing DLT. The DLT analysis set will be used for the analysis of DLT rates and for determining MTD.

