### **4.11.2 Efficacy Variables**

The analysis of clinical activity will be performed on the safety analysis set.

The following clinical responses will be investigated.

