#### **4.11.2.11 Prevention of secondary infections**

Proportion of patients with developed secondary infections will be computed together with its 95% score CI.

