| D-dimer, CPK, cardiac troponins, and ferritin                                         |                | Every 12h, as feasible                 |   |   |   |   |        |                     |                     |                     |                        | X                |            |

Abbreviations: AE: adverse events; AESI: adverse events of special interest; ARDS: acute respiratory distress syndrome; d: day(s); cfDNA: cell free DNA; CPK: creatine phosphokinase; CT: computed tomography; ECG: electrocardiogram; EOH: End-of-Hospitalization; F/U: Follow-up; HLA: human leukocyte antigen; h: hour (s); IL: interleukin; iNKT cells: invariant natural killer T cells; RT-PCR: reverse transcriptase polymerase chain reaction; SAE: serious adverse event; SOFA: sequential organ failure assessment; WOCBP: women of childbearing potential.

a End-of-Hospitalization is defined as patient discharge from hospital and/or death. If a patient is discharged at Day 30, 30-day Follow-up will be the same as EOH. After discharge, a patient will enter Safety Follow-up period and the patient will be contacted by telephone 3 and 6 months after discharge regarding any SAEs and to confirm survival, as feasible..

b In case of earlier discharge from the hospital, no visit is expected until 30-Day Follow-up.

c Performed before infusion of agenT-797 on D1. These samples will be obtained at the time of the routine labs blood draws.

d A complete examination, as feasible, will be performed at Screening and symptom-directed and medically indicated physical examinations are done thereafter.

e Vital signs include body temperature, heart rate, respiratory rate, systolic and diastolic blood pressure and are assessed by physician or nurse. On the day of infusion of agenT-797 (D1), measurements will be 15 min prior to infusion, and 15 min, 30 min, 1h, 2h, 3h, and 4h postinfusion.

- f ECG to be performed at Screening, Day 1 predose and EOH, 30-Day Follow-up, and at other times as clinically indicated.
- g Only AEs associated with study procedures and/or leading to withdrawal and all SAEs will be collected prior to study drug infusion. Patients are monitored for toxicities following infusion. All other AEs, SAEs, and AESIs will be collected in the Safety Follow-up period.

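### The time window for the secondary-infection proportion is undefined, the documents date follow-up both from discharge and from infusion, and the crude proportion ignores time at risk under either start.

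*Combined protocol and SAP*

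**What the plan says.** The exploratory objective is to evaluate whether the cells prevent secondary infections. One of its two estimators in SAP Table 2 is the proportion of patients who developed secondary "infections during follow-up period"; the table does not say when that period starts or ends. SAP 4.11.2.11 sets no window: "Proportion of patients with developed secondary infections will be computed together with its 95% score CI".

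On the denominator, SAP 4.11.2 states "The analysis of clinical activity will be performed on the safety analysis set", and SAP 4.5 says that this set "will include all patients who received agenT-797".

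On when follow-up starts, the documents differ:

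- **Discharge.** SAP Table 4 footnote a, repeated in protocol Table 3: "After discharge, a patient will enter Safety Follow-up period". Protocol synopsis: "Safety follow-up will occur 30 days after discharge".
- **Infusion.** Protocol 8.1.6 has all adverse events, serious or not, recorded from consent "through 30 days, and 6 months in the Safety Follow-up period, after infusion". Protocol 8.1.10 likewise counts its six months from infusion.
- **Implied infusion.** SAP Table 4 footnote g assigns all other adverse events to the Safety Follow-up period. That works only if the period covers the hospital stay.
- **Mixed.** Protocol 4.10 and SAP 3.9 give a 30-day period whose first visit is at Day 30 or at the end of hospitalization.

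End of hospitalization is discharge or death. Neither document gives person-time, censoring, or a rule for death before infection for this endpoint; SAP 4.11.1.1 says only that missing data are not imputed.

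**The concern.** Two programmers could follow the SAP faithfully and produce different counts. One would start at infusion and include infections acquired in intensive care. The other would take the schedule footnote literally and start at discharge. The second count would omit the period in which patients are ventilated and assessed daily. It would also treat every in-hospital death as infection-free, because such a patient never enters the window but remains in the denominator.

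The second problem does not depend on the start date. A proportion over all treated patients gives the same weight to someone observed for three days and someone observed for thirty. A patient who dies early has little chance to acquire an infection, so early deaths lower the proportion. An unfavourable outcome can then look like prevention, which is what the objective asks about. Differences between cohort percentages cannot be separated from differences in observed time.

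**Working it through.** **1. Reported figures.** Supplement Table S2 gives patients with infections as 3/3, 4/4 and 6/13 in Cohorts 1 to 3. The sums are 3 + 4 + 6 = 13 and 3 + 4 + 13 = 20, and 13/20 = 65.0%, which agrees with the table. The Wilson score 95% CIs, the method named in the SAP, are 43.3 to 81.9% overall, 43.9 to 100% (3/3), 51.0 to 100% (4/4) and 23.2 to 70.9% (6/13). The table gives no onset dates, discharge dates or patient-days. The figure under a stated window, or as a rate, therefore cannot be computed from the documents. Steps 2 to 4 are illustrations under stated assumptions.

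**2. Effect of the start date.** Suppose that some of the 13 had onset only before discharge. A count from discharge, over 20 treated, gives:

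| Onset only in hospital (assumed) | Counted | Proportion (Wilson 95% CI) |
|---|---|---|
| 0 | 13 | 65.0% (43.3 to 81.9) |
| 3 | 10 | 50.0% (29.9 to 70.1) |
| 7 | 6 | 30.0% (14.5 to 51.9) |
| 10 | 3 | 15.0% (5.2 to 36.0) |
| 13 | 0 | 0.0% (0.0 to 16.1) |

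In-hospital deaths also cap the result. If D of 20 die before discharge, the largest attainable proportion is (20 − D)/20: 80%, 70%, 60% or 50% for D = 4, 6, 8 or 10.

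**3. Time at risk, window from infusion to Day 30.** Assume a constant hazard that gives 65% by 30 days: h = −ln(1 − 0.65)/30 = 0.0350 per day, or 3.5 per 100 patient-days. Over 7 days the risk is 1 − exp(−7 × 0.0350) = 21.7%. If a share f of patients is at risk for only 7 days, for example through death, the crude proportion is (1 − f) × 65.0% + f × 21.7%:

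| f | Crude proportion | Rate per 100 patient-days |
|---|---|---|
| 0 | 65.0% | 3.5 |
| 20% | 56.3% | 3.5 |
| 30% | 52.0% | 3.5 |
| 40% | 47.7% | 3.5 |
| 50% | 43.4% | 3.5 |

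**4. Time at risk, counting in hospital only.** Assume a constant daily hazard h, an exponential stay with mean m, and nothing counted after discharge. The proportion infected is h/(h + 1/m), and the mean time at risk is 1/(h + 1/m).

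- h = 0.05: 0.05/0.15 = 33% for m = 10 days; 0.05/0.10 = 50% for m = 20 days.
- h = 0.03: 0.03/0.13 = 23%; 0.03/0.08 = 37%.

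The ratios are 1.5 and 1.6 at identical daily risk. Infections divided by time at risk return h each time: 5.0 and 3.0 per 100 patient-days.

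**5. Would a competing-risk curve help?** With the end of the stay (discharge or death) as the competing event, cumulative incidence at Day 30 is h/(h + 1/m) × [1 − exp(−30(h + 1/m))]. At h = 0.05 this is 0.333 × (1 − exp(−4.5)) = 33% for m = 10 and 0.500 × (1 − exp(−3.0)) = 48% for m = 20. The spread is almost unchanged. Of these measures, only the person-time rate removes it.

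**The case against.** A reader might infer that in-hospital infections are left out altogether. The documents do not support that. Table 2 speaks of a follow-up period, not of the Safety Follow-up period; SAP 4.11.2.11 restricts nothing; adverse events are collected continuously; and protocol 8.1.6 counts from infusion. Table S2 and the caption of Figure S5, which describes intensive-care patients with secondary infections, do not look like a post-discharge count, although without onset dates they prove nothing. What stands is the conflict between definitions.

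A reader might also infer that infections present at infusion would be counted, since exclusion 8b says "Patients on treatment and/or ongoing improvement with minor common infections (e.g., urinary tract infection, minor skin infections) are permitted to participate". SAP 4.11.4 largely answers this: pre-existing illness is not an adverse event unless it worsens, and treatment-emergent events must begin or worsen after dosing. Only a cross-reference from 4.11.2.11 is missing.

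Early discharge is a weaker example than early death. Under protocol 8.1.6 a discharged patient's events are still recorded to 30 days after infusion, and the Day 30 visit includes examination and laboratory tests. The figures in step 4 assume that nothing is counted after discharge, so they do not describe the infusion-based reading.

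Finally, the endpoint is exploratory, the trial is single-arm, no hypothesis is tested, and SAP 4.11.2.11 plans no cohort comparison. This limits the consequence. It does not remove the need to define a proportion that is offered as evidence on prevention.

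**Conclusion.** The point holds in this form: the window is undefined, the candidate definitions conflict, and one of them drops the hospital stay from the numerator while keeping everyone in the denominator. It is not shown that the analysis would use, or did use, that reading.

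The neglect of time at risk holds under either start date and is clearest for early deaths. In the illustration, 20 to 50% of patients with only 7 days at risk move the proportion from 65.0% to between 56.3% and 43.4% at an unchanged rate. With in-hospital counting alone, doubling the mean stay changes it by a factor of 1.5 to 1.6. These sizes rest on constant hazards and on assumed stays and death patterns; the documents give none of them.

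The cohort percentages in Table S2 (100%, 100% and 46.2%) may tempt a reader towards a dose-related protective effect, or towards an artefact of shorter observation. Without patient-days the documents support neither. No error rate or sample size is affected. The change is worth making because it settles what is counted at little cost.

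**What to change.** In SAP Table 2 and 4.11.2.11:

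- Replace the follow-up wording with a fixed window from infusion through Day 30, stated to include the hospital stay.
- Count only infections that meet the treatment-emergent rule in SAP 4.11.4, by cross-reference.
- Report first infections per 100 patient-days at risk, by dose level and overall. Time at risk runs from infusion to the earliest of first infection, death, withdrawal or Day 30.
- Show beside it the simple proportion with its score CI and the number who died uninfected.
- List later serious infections separately.

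A rate restricted to in-hospital days may be added, since risk and intensity of assessment may differ after discharge. A cumulative incidence with discharge as a competing event should not be offered as the remedy, because it keeps the dependence on length of stay.

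The cost is a SAP wording change and one extra table. Adverse-event onset dates, visit and completion dates and a listing of deaths are already planned. The rates will be imprecise in cohorts of 3 or 4 patients and should be presented as descriptive.

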## 4 STATISTICAL METHODS

### 4.1 Data Quality Assurance

All tables, figures and data listings to be included in the report will be independently checked for consistency, integrity and in accordance with standard procedures.

### 4.2 General Presentation Considerations

Baseline is defined as the last available pre-treatment assessment. The end of the study is defined as the date on which the last subject completes the final follow-up visit, which may be up to 6 months after the last subject's screening date. Treatment day will be calculated relative to the date of the first treatment day such that Treatment Day = Assessment Date – First Infusion Date + 1. 6

Continuous data will be summarized in terms of the mean, standard deviation (SD), median, upper quartile, lower quartile, minimum, maximum and number of observations, unless otherwise stated. The minimum and maximum will be reported to the same number of decimal places as the raw data recorded in the database. The mean, median, lower quartile and upper quartile will be reported to one more decimal place than the raw data recorded in the database. The SD will be reported to two more decimal places than the raw data recorded in the database. In general, the maximum number of decimal places reported shall be four for any summary statistic.

Categorical data will be summarized in terms of the number of patients providing data at the relevant time point (n), frequency counts and percentages.

Percentages will be presented to one decimal place. Percentages will not be presented for zero counts.

Changes from baseline in categorical data will be summarized using shift tables where appropriate.

P-values greater than or equal to 0.001, in general, will be presented to three decimal places. P-values less than 0.001 will be presented as “<0.001”.

Wilson confidence intervals (CIs) will be presented to one more decimal place than the raw data.

### 4.3 Software

All report outputs will be produced using SAS version 9.4 or later or R version 4.1.1 or later.

### 4.4 Study Patients

#### 4.4.1 Disposition of Patients

A clear accounting of the disposition of all patients who enter the study will be provided, from screening to study completion based on all subject analysis set, as defined in [Section 4.5](#).

The disposition summaries will include the following:

- Number and percentage of patients screened for entry into the study.
- Number and percentage of patients excluded by major reason.
- Number and percentage of patients treated (with at least one dose of study medication).
- Number and percentage of patients entering; withdrawing from study treatment; withdrawing from the study and completing each phase of the study by dose level and overall. Withdrawals from the study and from study treatment will also be summarized by major reason.

A by-subject listing of eligibility details, visit dates and withdrawal/study completion details (including reason for discontinuation and duration) will be provided.

#### 4.4.2 Protocol Deviations

Major protocol deviations are defined as those deviations from the protocol likely to have an impact on the efficacy and/or safety of study treatments. The impact of the major protocol deviations on the efficacy and/or safety results will be investigated by assessing the robustness of the study results and conclusions to the choice of analysis set, both including and excluding data potentially affected by major protocol deviations.

Major protocol deviations and any action to be taken regarding the exclusion of patients or affected data from specific analyses are defined in the project-specific protocol deviation specification.

All protocol deviations will be listed by subject.

### 4.5 Analysis Sets

Three subject analysis sets are defined for the study analyses, as follows:

- **The All Subject Analysis Set** will include all patients who have completed informed consent, irrespective of the study treatment administered. This analysis set will be used for the disposition summary and the listing of study populations.
- **The Safety Analysis Set** will include all patients who received agenT-797. This analysis dataset will be used for safety analysis and all listings other than listings of subject disposition and study populations.
- **The Dose-Limiting Toxicity Analysis Set** will include all patients who either experienced a DLT within 28-day observation or completed study treatment and 28-

day observation for DLT without experiencing DLT. The DLT analysis set will be used for the analysis of DLT rates and for determining MTD.

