## **4.7. STUDY CRITERIA**

### **4.7.1. Patient Inclusion Criteria**

For inclusion in this trial, all the following inclusion criteria must be fulfilled. No waivers to inclusion criteria will be permitted.

1. Voluntarily agree to participate and can provide informed consent or have a duly appointed health care proxy established which/who has the authority to consent on behalf of the patient
2.  $\geq 18$  years of age
3. Inpatient hospitalization
4. Evidence of SARS-CoV-2 infection with the diagnosis of moderate to severe ARDS per Berlin definition ([ARDS 2012](#)), no more than 2 weeks prior to study enrollment
5. Patients at high risk of intubation or intubated with mechanical ventilation
6. Female patients of childbearing potential must be willing to use highly effective contraception measures starting with the Screening visit through 90 days after last dose of study treatment. Male patients with a female partner(s) of childbearing potential must agree to use highly effective contraceptive measures throughout the trial starting with the Screening visit through 90 days after the last dose of study treatment is received. Males with pregnant partners must agree to use a condom; no additional method of contraception is required for the pregnant partner

Note: Abstinence is acceptable if this is the established and preferred contraception method for the patient

7. Patients, or study participant's duly appointed health care proxy with the authority to consent on behalf of the patient, must consent to placement of a central venous access line for the administration of agenT-797

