### **8.1.10. Reporting of Serious Adverse Events**

All SAEs must be reported from the time of ICF signature through 6 months in the Safety Follow-up period after infusion with agenT-797, and followed-up until resolution, if feasible.

All SAEs must be reported to the Sponsor within 24 hours of the first awareness of the event.

Any death, SAE, or pregnancy (including pregnancy of a partner) experienced by a patient regardless of relationship to study drug, or any death that occurs within 6 months after receiving study drug, must be promptly reported (within 24 hours of the Investigator becoming aware of the event) in the CRF and/or via email.

AESIs, even if they do not meet the serious criteria, must be reported using the SAE form and in an expedited manner (within 24 hours of the Investigator becoming aware of the event), but should be noted as non-serious on the SAE form and the AE CRF ([Section 8.1.3](#)).

The Investigator must complete, sign and date the SAE pages, verify the accuracy of the information recorded on the SAE pages with the corresponding source documents.

For overdoses associated with a SAE, standard reporting timelines apply ([Section 8.1.6](#)).

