### **4.11.4 Adverse Events**

An AE is any untoward medical occurrence in a study subject administered an investigational medicinal product (IMP) which does not necessarily have a causal relationship with this treatment. An AE can therefore be any unfavorable and unintended sign (including a clinically significant abnormal laboratory finding), symptom, or disease temporally associated with the use of an IMP, whether or not considered related to the IMP. Adverse events may include the onset of new illness and the exacerbation of pre-existing conditions.

Other untoward events occurring in the framework of a clinical study will be recorded as AEs, e.g. those occurring during treatment-free periods (including screening or post-treatment follow-up periods), in association with study-related procedures and assessments.

Concomitant illnesses, which existed before entry into the clinical study, will not be considered AEs unless they worsen during the treatment period. Pre-existing conditions will be recorded as part of the subject's medical history.

A treatment-emergent adverse event (TEAE) is defined as an AE that begins or that worsens in severity after at least one dose of the study drug has been administered.

Any AEs with incomplete start and end dates/times will be treated as follows:

Adverse events with unknown start and/or end times (but where the date is known) will be imputed with a time of 00:00 h for the tabulations but will be shown as NK: NK in the listings (where NK = Not Known).

Adverse events with completely unknown start dates will be considered as treatment-emergent for the tabulations and will be shown as NK in the listings. Partially complete AE dates will not be imputed in the listings and the available day, month and year components will be used to determine if an adverse event is treatment-emergent taking the first dosing date and end of study date as references.

Adverse events will be coded using the MedDRA version 22.0 or higher.

The relationship or association of the study medication in causing or contributing to the AE will be characterized by the Investigator using the following classification and criteria:

- Possibly or probably related: A clinical event, including laboratory test abnormality, with a reasonable time sequence to study medication administration that might or might not be also explained by concurrent disease or other drugs or chemicals.

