- Not related: A clinical event, including laboratory test abnormality, judged to be clearly and incontrovertibly due to extraneous causes (e.g., diseases, environment), or with a temporal relationship to study medication administration that makes a causal relationship improbable, and/or for which other drugs, chemicals, or underlying diseases provide a much more plausible explanation.

Severity or intensity will be assessed according to the NCI CTCAE version 5.0 severity grading scale. Grade refers to the severity of the AE. The NCI CTCAE version 5.0 displays Grades 1 through 5 with unique clinical descriptions of severity for each AE based on this general guideline:

- Grade 1: Mild (awareness of sign or symptom, but easily tolerated)
- Grade 2: Moderate (discomfort sufficient to cause interference with normal activities)
- Grade 3: Severe (incapacitating, with inability to perform normal activities)
- Grade 4: Life-threatening (urgent intervention indicated)
- Grade 5: Death related to AE.

The following summaries will be generated based on safety analysis set by dose level and overall:

- A summary of the number and percentage of patients reporting an AE by SOC and PT.
- A summary of the number and percentage of patients reporting a TEAE by SOC and PT.
- A summary of the number and percentage of patients reporting a related TEAE by SOC and PT.
- A summary of the number and percentage of patients reporting a TEAE by severity, SOC and PT.
- A summary of the number and percentage of patients reporting a TEAE by causality, SOC and PT.

AE summaries will be ordered in terms of decreasing frequency for SOC, and PT within SOC, in the overall group, and then alphabetically for SOC, and PT within SOC.

For each subject and each adverse event, the worst severity recorded will be attributed and used in the by-severity summaries. Similarly, the worst causality (most related to treatment) will be attributed and used in the by-causality summaries. If severity or causality is missing, a conservative approach for AE assessment (taking into account the worst case) will be followed.

A by-subject listing of all AEs (including non-treatment-emergent events) will be provided. This listing will be presented by dose level and will include center, subject identifier, age, sex, race, adverse event (SOC, PT, and verbatim term), date of onset, date of resolution, duration, severity, seriousness, action taken, outcome and causality.

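### Adverse events, serious adverse events and deaths before infusion in patients who are then never infused appear in no AE, SAE or death table or listing

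*Combined protocol and SAP*

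**What the plan says.** **Collection starts at consent.** Protocol 8.1.10 states: "All SAEs must be reported from the time of ICF signature through 6 months in the Safety Follow-up period after infusion with agenT-797". For AEs in general there are two statements. Protocol 8.1.6 is the broad one: "All AEs, non-serious and serious, related or unrelated, need to be recorded from the time of ICF signature through 30 days". Footnote g of the schedule of assessments (protocol Table 3, SAP Table 4) is narrower: "Only AEs associated with study procedures and/or leading to withdrawal and all SAEs will be collected prior to study drug infusion". SAP 4.11.4 also counts as AEs untoward events such as "those occurring during treatment-free periods (including screening or post-treatment follow-up periods), in association with study-related procedures and assessments".

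**Reporting starts at infusion, by choice of analysis set.** SAP 4.5 limits the Safety Analysis Set to infused patients and adds: "This analysis dataset will be used for safety analysis and all listings other than listings of subject disposition and study populations". Protocol 9.1 and SAP 4.11.3 assign safety analyses to the same set, apart from DLT rate and MTD. The All Subject Analysis Set (everyone who consented) is used only for the disposition summary and the listing of study populations.

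**The broadest listing.** SAP 4.11.4 promises: "A by-subject listing of all AEs (including non-treatment-emergent events) will be provided. This listing will be presented by dose level".

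**The concern.** The plan asks sites to record a class of event and then sets a reporting rule that cannot show part of it. If a patient is withdrawn before the single infusion because of an AE, that patient lies outside the Safety Analysis Set by definition. The same is true of a patient who dies, or has a serious or procedure-related event, after consent and is never infused.

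The patients have moderate to severe ARDS, and protocol 4.5.5 allows screening in the 4 days before infusion. Some trial-related steps come before the product is given. The clearest is the central line: under protocol 4.7.1 the patient or proxy "must consent to placement of a central venous access line for the administration of agenT-797". A complication serious enough to prevent infusion is the kind of event a reader would want to see, and the planned outputs would leave it out.

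**Working it through.** No arithmetic decides this point. The check takes each planned output, finds its analysis set, and asks whether a patient who consented but was never infused can appear in it.

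**Step 1: what is collected before infusion.** Protocol 8.1.6 and footnote g differ in breadth. SAEs, procedure-related AEs and AEs leading to withdrawal are collected under either, so the point does not depend on which governs.

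**Step 2: where each output draws its patients.**

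| Output (SAP section) | Analysis set | Uninfused patient included? |
|---|---|---|
| AE and TEAE summaries (4.11.4) | Safety, named | No |
| By-subject listing of all AEs (4.11.4) | None named; Safety by the 4.5 rule; laid out by dose level | No |
| Death summary (4.11.5) | Safety, named | No |
| Serious TEAE summary (4.11.5) | Safety, named; post-dose events only | No |
| Serious TEAE listing (4.11.5) | None named; Safety by the 4.5 rule; post-dose events only | No |
| Death listing (4.11.5) | None named; Safety by the 4.5 rule | No |
| 30-day and 6-month mortality (4.11.2) | Safety, named | No |
| TEAEs in the DLT period (4.11.6) | DLT | No |
| Disposition summary and listing (4.4.1) | All Subject | Yes, as a reason for exclusion or discontinuation |

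The DLT row is the only safety output in the table on a set other than the Safety Analysis Set. As defined, that set adds no uninfused patient.

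**Step 3: does the listing of all AEs close the gap?** It includes non-treatment-emergent events, so it shows a pre-infusion event in a patient who was later infused. The 4.5 rule keeps out anyone never infused, and the layout by dose level gives such a patient no place.

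**Step 4: does disposition close the gap?** SAP 4.4.1 gives eligibility details, visit dates and withdrawal or completion details with the reason. It does not call for event term, grade, seriousness or causality.

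**Result.** AE, SAE or death outputs that include a consented, never-infused patient: none.

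**The case against.** The strongest reply is that a treated-patient set is the normal choice and fits the primary objective, which is the safety of the infusion. That stands for the rate tables, and the fix leaves them alone. It does not explain why by-subject listings of collected events should also stop at infused patients.

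Several limits on the point also stand, and each blocks a stronger reading.

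- *That pre-infusion harm disappears altogether.* It does not. SAP 4.11.4 plans an AE summary separate from the TEAE summary, plus the listing with non-treatment-emergent events. Pre-infusion events in patients later infused can be seen.
- *That the safety of trial procedures as a whole is conditional on reaching infusion.* Lavage is limited to intubated patients with a clinical reason for it, and brushing is done when possible. Most scheduled time points for both fall after infusion, where the AE outputs cover them. The central line is the better example.
- *That a number of lost patients can be stated.* Assume that 10% to 20% of consented patients are not infused, a rate the documents do not give. With 43 infused, 43/0.9 − 43 = 4.8 and 43/0.8 − 43 = 10.8. But 43 is a ceiling. With the 20 patients in Table S2, 20/0.9 − 20 = 2.2 and 20/0.8 − 20 = 5.0. Both ranges count patients, including plain screen failures, and not events.
- *That a mortality comparison is distorted.* The protocol says only that a matched control may be used, and the SAP defines none. Mortality would stay on the Safety Analysis Set, so a wider listing would not change that estimate.
- *That participants are less protected.* SAEs and deaths still go to the sponsor within 24 hours, and the Safety Monitoring Committee reviews safety data from enrolled patients.

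**Conclusion.** The point holds as a gap in the planned report. SAP 4.5 states a rule that excludes harm data the trial has already collected, for one group: patients with an event between consent and infusion who are never infused. For them, no AE, SAE or death table or listing carries the event, and disposition carries at most a reason.

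The size cannot be computed. The number of consented but uninfused patients is not in the documents, nor is the number of them with any event; it may be small or zero. No post-infusion rate, DLT decision or expedited report changes. The change is still worth making, because the omission follows from the written rule and is inexpensive to remove.

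The conclusion rests on reading the 4.5 rule literally for the listings that name no set of their own. If the sponsor means the AE and death listings to cover all consented patients, the SAP needs to say so.

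**What to change.** In SAP 4.5, 4.11.4 and 4.11.5, base the by-subject listings of AEs, SAEs (including those with onset before infusion) and deaths on the All Subject Analysis Set, with a 'not infused' group beside the dose levels. As a smaller alternative, add one listing on that set of AEs, SAEs and deaths from consent to infusion, with the same group.

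Keep the Safety Analysis Set for the TEAE, death-rate and dose-level tables, and the DLT set for the DLT outputs.

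The cost is SAP wording and one wider or extra listing. The data are already collected and no study procedure changes. Protocol 9.5 allows such a change to be documented in the final SAP or the clinical study report.
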